#### Cervical sample collection

The collection of cervical samples will be performed in the routine of care at 18 primary health care units in Indaiatuba. The cervical sample will be collected using a brush, and the sample will be stored in a previously identified vial containing preservative medium specific for the HPV test (PreservCyt, ThinPrep – Hologic, Inc., Marbourough, MA, USA). All procedures related to sample collection, storage, and transportation to the HPV testing laboratory are similar to those used in previous cytology screening, except for sample slides (conventional cytology) replaced for liquid-based cytology (LBC) vials.

All primary health care units will be informed about CCSP-HPV guidelines on the collection, storage, and transportation of samples, which will be primarily sent to a central unit in the city and from there to the HPV testing laboratory. This sample transport is planned to take place within one week. The samples can be well kept for up to 6 weeks at room temperature of 15 to 30 degrees Celsius.

#### Liquid-based cytology

In cases of positive tests for the other 12 hr-HPV types, the cytology evaluation and results will follow the Bethesda System Classification 2014. Considering that cervical cytology has a very variable sensitivity for the detection of HSIL, in this study protocol, the cytologists will have prior information on HPV results (tested positive for other 12 hr-HPV types). The strategy is to increase attention to the smallest morphological details and thus increase the sensitivity of the cytology test.

#### Colposcopy and cervical procedures

The colposcopy evaluation will be performed at a referral unit in Indaiatuba, and the indication will be defined according to the CCSP-HPV flowchart (Fig. 1). The colposcopy will follow the standards preconized for the Brazilian Society of Pathology of Lower Genital Tract and Colposcopy and the International Federation of Cervical Pathology and Colposcopy (IFCPC). The colposcopic images will be described and classified according to the lastest colposcopic terminology [27].

The colposcopy unit has two active colposcopists, and they will be informed about the program and to perform colposcopy in cases with positive HPV test results, with or without previous cytology evaluation, a novelty in the routine of these professionals. Previously, these colposcopists will be undergoing a comprehensive test with 20 to 40 colposcopic cases with illustrations to assess the agreement of colposcopic findings with two additional senior colposcopists at Women’s Hospital (UNICAMP). The training will be repeated until the colposcopists reach a good or excellent level in agreement tests. The evaluation of the cervical canal will be performed whenever indicated, according to current guidelines, consisting of cervical canal cytological samples or excision procedures [28]. The cervical biopsy will be guided for colposcopy using biopsy surgical tweezers to take a tissue sample from the suspected area of cervical epithelium, usually 3 to 5 mm in size. In the absence of colposcopic changes, no biopsy will be performed.

Surgical procedures for excision of the transformation zone (EZT) will be performed for diagnostic purposes in women with or suspected HSIL. EZT will be performed using a loop electrosurgical procedure in the same colposcopy unit. In specific clinical situations, the surgical procedure in the cervix will be performed at City Hospital and, exceptionally, by cold knife conization. The Women’s Hospital (UNICAMP) is the reference for more comprehensive support for cervical cancer cases if it occurs in the current organization.

#### Histopathological evaluation

The histopathological evaluation will be performed on cervical tissue samples obtained by biopsies or excision procedures. The pathology laboratory available to serve the routine of the Indaiatuba Health Department will be responsible for this exam. For quality assurance, all biopsies will be tested for p16 immunohistochemistry in an external laboratory. For discrepant or doubt diagnoses, a senior pathologist from the University of Campinas (UNICAMP) will review and the final histologic diagnosis will be established by consensus among pathologists and according to the WHO classification [29].

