**Methods:**

The CCSP-HPV was designed based on successful guidelines that replaced cervical cytology-based screening by the DNA-HPV test performed at 5-year intervals. The screening will be performed for the female population aged 25-64 years cared for by the public health system and aim to reach 80% coverage after completing the first round. The chosen DNA-HPV test detects 14 hr-HPV types and genotypes HPV-16 and 18. All women with a negative test will be reassessed after five years. Women showing a positive test for HPV-16 and/or 18 will be referred for colposcopy. Those showing the other 12 hr-HPV types will be tested by cytology, and if any abnormality is detected, they will also be referred for colposcopy. The histopathologic evaluation will be reviewed by a pathologist panel and aided by p16 immunohistochemistry. A cost-effectiveness analysis will be performed by a Markov model comparing the cost of the new program and the screening performed by conventional cytology five years prior (2011–2016).

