### Eligibility

Inclusion criteria for CCSP-HPV
women have started sexual activity aged 25 to 64 years are the target for regular screening test (women over 64 years will be permitted for a single exit test by personal request);women physically well enough to undergo a pelvic exam.

The inclusion criteria evaluation should be postponed if any of the following conditions are met: 40 days postpartum period, abundant genital bleeding, cervicovaginal infection and having underwent the last cervical cytology in the last 12 months.

Exclusion criteria
women who have already undergone DNA-HPV testing for different medical purposes except screening;women with a previous diagnosis of the cervical lesion followed in specialized clinics;women who underwent a total hysterectomy.

Control group:
All women from Indaiatuba that underwent cytology tests by SUS from 2012 to 2016. These women will be identified from the regional central laboratory database, located at the Cytopathology Laboratory of Women’s Hospital (University of Campinas - UNICAMP). All information about the compliance of the staff to follow the official recommendations related to conducting the women with abnormal pap, as the follow-up and/or treatment, are available at Colposcopy Unit in Indaiatuba City and Women’s Hospital (UNICAMP).

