### Data analysis

Women’s information and test results will be entered into a single Excel database for the entire municipality. Some information will also be present in the Integrated Health Informatics System of Indaiatuba (SALUS System), which is a health management system for the entire city. A more detailed information system for monitoring screening population management according to the flowchart proposed for the CCSP-HPV protocol (schedule for sample collection, including follow-up cervical cytology and/or colposcopy, DNA-HPV test results, colposcopy, biopsy, EZT, and test repetition) is in development, which will be integrated into the SALUS System. Information will be discriminated for every primary health care unit. Thus, we will have the opportunity to monitor and identify areas with adequate population coverage and areas that need further action to achieve adequate coverage.

The databases with information generated from this protocol will be revised and analyzed annually and after the study ends. During the five years planned for the study, women inclusion and additional health procedures for those with positive HPV testing will be monitored every 30 days.

A cost-effectiveness survey is planned for this study, and it will be compared with the screening performed by conventional cervical cytology five years prior. Such analysis will also consider the diagnostic rates of precursor lesions and cervical cancer corresponding to the HPV test or cervical cytology-based periods. Indaiatuba public health system and regional health service (Women’s Hospital, UNICAMP) records will be reviewed looking for cases of HSIL, AIS or cervical cancer diagnosed and managed out of the screening set in women from Indaiatuba.

For cost-effectiveness analyses, the Markov model will be built, and the detailed process will be subject to future publication. Cost information regarding the screening process will be collected for the previous cytology screening and during the implementation of the new program.

Qualitative analysis is also foreseen to evaluate the perception of the population and health professionals regarding the modification of the method of cervical cancer screening in the city.

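### HPV-period lesions are diagnosed with p16, selective consensus review and tested colposcopists, control lesions are taken from existing records, so the lesion-rate comparison may mix a change of diagnostic standard with the effect of the HPV test

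*Protocol article*

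**What the plan says.** **HPV period.** The section on histopathological evaluation makes the Indaiatuba Health Department's routine pathology laboratory responsible for reading the tissue. It then adds p16: "For quality assurance, all biopsies will be tested for p16 immunohistochemistry in an external laboratory". Review is selective: "For discrepant or doubt diagnoses, a senior pathologist from the University of Campinas (UNICAMP) will review", after which the final diagnosis is settled by consensus. The Abstract summarises this as "The histopathologic evaluation will be reviewed by a pathologist panel and aided by p16 immunohistochemistry". The section on colposcopy describes a test on 20 to 40 illustrated cases against two senior colposcopists, and "The training will be repeated until the colposcopists reach a good or excellent level in agreement tests". It also says that no biopsy is taken when colposcopy shows no change.

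**Control period.** Under Eligibility the control group is "All women from Indaiatuba that underwent cytology tests by SUS from 2012 to 2016". On the source of the data: "These women will be identified from the regional central laboratory database". Follow-up and treatment information is held at the colposcopy unit and at Women's Hospital. No re-reading, p16 staining or review of control biopsies is described, and the article does not say how those biopsies were read at the time.

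**Comparison.** Under Data analysis, the cost-effectiveness work compares the new programme with the earlier cytology screening, and "Such analysis will also consider the diagnostic rates of precursor lesions and cervical cancer corresponding to the HPV test or cervical cytology-based periods". Lesions identified and treated are listed among the endpoints that feed it.

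**The concern.** A detection rate depends on the screening test, on who is biopsied, and on where the pathologist draws the line for HSIL. The article changes the first by design. It also describes added steps for the other two in the HPV period only. If p16 and consensus move the HSIL threshold, or if tested and trained colposcopists biopsy differently, the lesion rate changes even when the two screening tests would have found the same disease.

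That change would pass into the detection inputs of the cost-effectiveness model. It matters for attribution because the Abstract's discussion offers the results to other places deciding whether to adopt DNA-HPV screening. A place that adopts the test without p16 and consensus review could not carry the estimate over. The problem also cannot be repaired later if only the final diagnosis is stored.

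**Working it through.** **1. The plan's own figure.** 63,362 women × 0.50 = 31,681 relying only on SUS. 31,681 × 0.80 = 25,345, or 25,345 / 5 = 5,069 a year. This reproduces the stated 25,000 women and 5,000 a year to rounding. It is a coverage target. The article gives no HSIL rate, effect size, alpha or power, so it contains no figure from which the bias could be computed.

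**2. The two periods side by side.**

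| Step | HPV period | 2012–2016 |
|---|---|---|
| Choice of biopsy | Colposcopists tested, training repeated until agreement is adequate | Not described |
| First reading | Routine laboratory | Not described; existing records |
| p16 | All biopsies, external laboratory | Not described |
| Review | Discrepant or doubtful diagnoses, consensus | Not described |

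Cytologists in the HPV period also know the HPV result when they read the triage sample. I leave that out, because it belongs to the screening algorithm under evaluation.

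**3. How reclassification enters.** Let H be the number of HSIL diagnoses on the routine reading, d the share of H that p16 and review downgrade, and u the number upgraded into HSIL as a share of H. The recorded number is H × (1 − d + u). With no true difference between periods, and control diagnoses on the routine standard, the recorded rate ratio is f = 1 − d + u.

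- d = 0.20, u = 0: f = 0.80.
- d = 0, u = 0.20: f = 1.20.
- d = 0.10, u = 0.10: f = 1.00, although many individual diagnoses changed.

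Only the net change matters, and nothing in the article fixes d or u.

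**4. Illustration, on assumptions.** Assume a routine HSIL rate of 1%, 25,000 HPV-period women, 20,000 or 50,000 control women (the article counts tests, not women), no true difference, and a two-sided 5% test. Expected cases on the routine standard: 25,000 × 0.01 = 250. The chance of a nominally significant but spurious difference is Φ[(|p1 − p2| − 1.96 × SE0) / SE1], where SE0 uses the pooled rate and SE1 the separate rates.

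For f = 1.2 and 20,000 controls: p1 = 0.012, p2 = 0.010, pooled rate (300 + 200) / 45,000 = 0.01111, SE0 = 0.000994, SE1 = 0.000985. The argument is (0.00200 − 0.00195) / 0.000985 ≈ 0.05, which gives 0.52.

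| f | Recorded cases | Chance, 20,000 controls | Chance, 50,000 controls |
|---|---|---|---|
| 0.8 | 200 | 0.611 | 0.774 |
| 0.9 | 225 | 0.193 | 0.257 |
| 1.1 | 275 | 0.175 | 0.251 |
| 1.2 | 300 | 0.521 | 0.704 |
| 1.3 | 325 | 0.841 | 0.953 |

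For assumed rates of 0.5% to 1.5% the chance runs from 0.11 to 0.99. The table shows that a moderate net shift would be visible at this study size. It does not estimate the shift.

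**The case against.** **The control standard is inferred.** This stands. The article does not say how 2012–2016 biopsies were read. A reader might infer that the two periods certainly used different standards. The text supports only that the added steps are described for one period and that the other relies on existing records.

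**The aim is programme against programme.** This stands in part. The Abstract and the section on data analysis compare the new programme with earlier screening. For that question p16, consensus and colposcopist training can count as parts of what was delivered, and the final diagnosis is a proper outcome. Replacing it in the main comparison would be debatable and could detach the lesions counted from the treatment costs incurred. The concern applies where a lesion-rate difference is credited to the HPV test.

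**The Markov model is deferred to a later publication.** True, and adjustments may appear there. But a later paper cannot recover a routine reading that was not kept.

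**The Abstract contradicts the histology section on who is reviewed.** A reader might infer this from "The histopathologic evaluation will be reviewed by a pathologist panel and aided by p16 immunohistochemistry". The Abstract does not say that every case is reviewed. One sentence there condenses a procedure that the body spells out, and I do not count it as an error.

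**Selective review pushes the count one way.** A reader might infer this too. The article sends discrepant or doubtful diagnoses to review without limiting them to upgrades or downgrades, so the direction is open.

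**Conclusion.** The point holds in a limited form. As described, the between-period comparison of precursor-lesion rates may combine a change in diagnostic standard with the effect of the HPV test. Direction and size are unknown. Factors such as 0.80 or 1.20 are assumptions; if 10–20% of HSIL calls change, those extremes arise only when 20% change and all in the same direction, and offsetting changes bring the factor close to 1.

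The conclusion rests on one inference, that 2012–2016 diagnoses were made without the added steps. If the records show that p16 or review was already in use, the histology part shrinks or disappears. The whole-programme comparison is not invalidated. The weakness is worth correcting because it bears on what can be credited to the test and costs little to address while the routine reading can still be kept.

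**What to change.** 1. Store the routine laboratory's diagnosis, made before p16 and review, as a separate locked field beside the final diagnosis. This should be feasible, because the routine laboratory reads the tissue and an external laboratory does the p16. For biopsies already reported since the October 2017 start, take it from the laboratory's reports where they show it.
2. Establish from the records, and state, which histology standard applied in 2012–2016.
3. Keep the final diagnosis for the whole-programme comparison and its costs.
4. Prespecify a like-for-like comparison of lesion rates using the routine diagnosis in both periods, with a matching sensitivity analysis in the cost-effectiveness model and a cross-tabulation of routine against final diagnosis. Fix this before the interim cost-effectiveness analyses announced in the Discussion.
5. Credit a lesion-rate difference to the HPV test only if it holds in the like-for-like analysis.
6. State the difference in colposcopy training as a remaining limitation. It affects which women and which sites are biopsied, and keeping the routine histology reading does not remove it.

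The cost is one database field and one extra table, with no new slides or readers. The downside is that the added comparison rests on a less refined diagnosis.

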#### Follow-up

This study protocol will evaluate one round of HPV (five years). Women with positive tests and forwarded colposcopy will return to routine screening 5-year intervals after a colposcopic evaluation is negative and a 12-month follow-up DNA-HPV test is negative. This process will be repeated yearly until the tests become negative. Management and follow-up of HSIL or cancer diagnosis will be guided by the guidelines from the Brazilian National Cancer Institute [28].

### Endpoints

The endpoints of this study protocol include age compliance of the CCSP-HPV, the coverage rate of the target population, frequency of HPV positivity by age group, including 25-29 years old, number of colposcopies generated, and cervical lesions identified and treated. These data will be included in cost-effectiveness analyses based on appropriate and specific endpoints.

### Data analysis

Women’s information and test results will be entered into a single Excel database for the entire municipality. Some information will also be present in the Integrated Health Informatics System of Indaiatuba (SALUS System), which is a health management system for the entire city. A more detailed information system for monitoring screening population management according to the flowchart proposed for the CCSP-HPV protocol (schedule for sample collection, including follow-up cervical cytology and/or colposcopy, DNA-HPV test results, colposcopy, biopsy, EZT, and test repetition) is in development, which will be integrated into the SALUS System. Information will be discriminated for every primary health care unit. Thus, we will have the opportunity to monitor and identify areas with adequate population coverage and areas that need further action to achieve adequate coverage.

The databases with information generated from this protocol will be revised and analyzed annually and after the study ends. During the five years planned for the study, women inclusion and additional health procedures for those with positive HPV testing will be monitored every 30 days.

A cost-effectiveness survey is planned for this study, and it will be compared with the screening performed by conventional cervical cytology five years prior. Such analysis will also consider the diagnostic rates of precursor lesions and cervical cancer corresponding to the HPV test or cervical cytology-based periods. Indaiatuba public health system and regional health service (Women’s Hospital, UNICAMP) records will be reviewed looking for cases of HSIL, AIS or cervical cancer diagnosed and managed out of the screening set in women from Indaiatuba.

For cost-effectiveness analyses, the Markov model will be built, and the detailed process will be subject to future publication. Cost information regarding the screening process will be collected for the previous cytology screening and during the implementation of the new program.

Qualitative analysis is also foreseen to evaluate the perception of the population and health professionals regarding the modification of the method of cervical cancer screening in the city.

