The DNA-HPV test has a negative predictive value of approximately 100% and allows a screening interval of at least five years, longer than the 3-year interval for cytology. These would reduce the total number of tests performed, affecting costs. Some studies have provided strong evidence for the adoption of the DNA-HPV test in cervical cancer screening [11–14].

The Food and Drug Administration (FDA), in April 2014, approved the DNA-HPV testing that includes genotypes 16 and 18 (Cobas® HPV) for primary screening of cervical cancer [15]. More recently, the Society of Gynecological Oncology and the American Society of Colposcopy and Cervical Pathology have proposed a guideline for cervical cancer screening based solely on the use of DNA-HPV tests for women over 25 years of age [16]. Australia also approved the primary screening of HPV, with colposcopic evaluation for HPV 16/18 and reflex cytology for other types of HPV, starting at 25 years of age and at intervals of five years when the result is negative for HPV [17].

Cervical cancer is the third most common cancer among women in Brazil, with an estimated 16,350 new cases in 2018 [18]. Current recommendations from the Brazilian Ministry of Health state that cervical cancer screening is based on cervical cytology, which should be repeated every 3 years after two consecutive annual negative examinations, in women aged 25-64 years [19]. Data show an excess of cytology due to the opportunistic screening currently practiced in Brazil, with approximately 50% of cervical cytology performed annually and only 10% within a three-year interval recommended by the Brazilian protocols. Additionally, approximately 20% of screening tests are performed on women under 25 years of age [20, 21]. Besides, there is a large proportion of cases diagnosed at advanced stages, most of them managed at Public Health System [21, 22]. These factors highlight the need for reassessment of the cervical cancer screening program currently in place in Brazil.

In 2017, the city of Indaiatuba, in São Paulo State, was the pioneer in Brazil deciding to replace cervical cytology with the primary DNA-HPV test for primary cervical cancer screening. This paper aims to describe the implementation of the *Cervical Cancer Screening Program with Primary DNA-HPV testing (CCSP-HPV)*, the strategies designed to reach higher population coverage, and a study protocol for the cost-effectiveness analyses.

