#### Sample size calculation

The female population 25-64 years old comprises 63,362 subjects for Indaiatuba, according to the official Brazilian Census (2010) and estimates for 2014 [24]. In Brazil, health care is free of charge to every citizen, although some people co-use private services. In Indaiatuba, around 50% of the female population uses private services, and the other half relies exclusively on the SUS to access health care. Therefore, the target SUS population was 31,681women for the new program. As the goal of the program is to reach at least 80% coverage of the target population after five years, the population of the study was estimated to be 25,000 women in five years, which means at least 5000 women tested per year.

The organization of the CCSP-HPV implies developing strategies to reach higher target population coverage, evaluate the compliance of the staff to the program, and research to evaluate the cost-effectiveness. For comparison, a similar population from the same city that performed routine cytology screening from 2012 to 2016, five years before CCSP-HPV will be the reference for comparison of cost-effectiveness evaluation. This reference population (years 2012–2016) performed nine to eleven thousand pap tests per year (total 54,000 to 66,000 tests), but with a low agreement, about 33%, with the official recommendations for pap screening.

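### The HPV-versus-cytology comparison of lesion and cancer rates sets controls of any age against a programme aimed at ages 25-64, with no age restriction or adjustment stated

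*Protocol article*

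**What the plan says.** The study is a before/after comparison within one city. Under Data analysis, the cost-effectiveness work is to be set against the earlier conventional cytology screening, and "Such analysis will also consider the diagnostic rates of precursor lesions and cervical cancer corresponding to the HPV test or cervical cytology-based periods". For the model itself, "the Markov model will be built, and the detailed process will be subject to future publication".

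The two populations are defined under Eligibility. For the HPV programme, "women have started sexual activity aged 25 to 64 years are the target for regular screening test", with a one-off test on request above 64. The control group is "All women from Indaiatuba that underwent cytology tests by SUS from 2012 to 2016", and no age range is attached. The Sample size calculation section describes the reference as "a similar population from the same city that performed routine cytology screening from 2012 to 2016", again without mentioning age.

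Age appears in three other places:
- Endpoints lists "frequency of HPV positivity by age group, including 25-29 years old". The endpoint on cervical lesions identified and treated carries no age split.
- The Discussion plans to compare women aged 25-29 with older women, within the HPV programme only.
- Background reports that under opportunistic screening in Brazil "approximately 20% of screening tests are performed on women under 25 years of age", and the Discussion reports that 99.1% of the 7362 first-year HPV tests were in women aged 25-64.

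**The concern.** The risk of a precursor lesion or cancer depends on age. If the two periods contain different ages, a difference in their overall rates can arise even when each age group has the same rate in both. Here the difference in ages is built into the stated definitions: one group is bounded at 25-64 and the other is not.

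A second, less certain source lies within 25-64. The programme includes "developing strategies to reach higher target population coverage". The Discussion puts regional cytology coverage at 15 to 30%, against a programme goal of 80%. A programme meant to reach women who did not attend before may well change the age mix of attenders, although the article does not say how.

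The rates from this comparison are to inform the cost-effectiveness analysis. An age artefact in them would appear there as a gain or loss in effectiveness of the HPV programme.

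**Working it through.** **The plan's own figure.** The article gives no expected rates and no power calculation for the period comparison. Its one derived population figure concerns the HPV side: 63,362 women aged 25-64 x 0.5 relying on SUS = 31,681; x 0.80 coverage = 25,345. The stated 25,000 is reproduced to within 1.4%. This confirms that the HPV side is sized on ages 25-64.

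**Inputs for the age check.**
- Share of HPV tests within 25-64: 0.991, so 0.009 outside (Discussion, first 12 months).
- u, the share of cytology tests in women under 25: 0.20 (Background). This is a national figure, so 0.10 and 0.30 are also shown.
- f, the rate outside 25-64 divided by the rate within 25-64: not in the article. Assumed from 0 to 1.5.

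**Formula.** Set the rate within 25-64 to 1 in both periods and the rate outside it to f in both, so that there is no true difference at any age:

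crude ratio HPV/cytology = (0.991 + 0.009f) / ((1 - u) + u x f)

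At u = 0.20:
- f = 0: 0.991 / 0.80 = 1.24
- f = 0.5: 0.9955 / 0.90 = 1.11
- f = 1.5: 1.0045 / 1.10 = 0.91

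| f (assumed) | u = 10% | u = 20% | u = 30% |
|---|---|---|---|
| 0 | 1.10 | 1.24 | 1.42 |
| 0.25 | 1.07 | 1.17 | 1.28 |
| 0.5 | 1.05 | 1.11 | 1.17 |
| 1 | 1.00 | 1.00 | 1.00 |
| 1.5 | 0.96 | 0.91 | 0.87 |

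The true ratio is 1.00 in every cell. The calculation is per test, counts only under-25s as out of range on the cytology side, and uses one f for all out-of-range tests.

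**Mix within 25-64 (all inputs assumed).** Let k be the rate at 25-34 divided by the rate at 35-64, and let the share aged 25-34 be s0 under cytology and s1 under HPV. Then the ratio is (s1 x k + 1 - s1) / (s0 x k + 1 - s0).
- k = 2, share falling from 35% to 25%: 1.25 / 1.35 = 0.93
- k = 2, share rising from 25% to 35%: 1.35 / 1.25 = 1.08
- k = 3, same shifts: 1.50 / 1.70 = 0.88 and 1.70 / 1.50 = 1.13

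The article documents neither k nor the shares. These figures show only that an age limit alone need not remove the problem.

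**After the fix.** With both periods restricted to 25-64 and standardised to the same age weights, equal age-specific rates give a ratio of 1.00 by construction.

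**The case against.** The strongest objection is that the article names no estimator. It does not call the rates crude or say that age will be ignored, and it defers the model detail to a later paper. Age standardisation is something an article commonly leaves to the full protocol or analysis plan. That stands as far as it goes: the absence of a named adjustment method is not in itself an error. It does not cover the control group, which the article does define, and defines without the age range it gives the programme.

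A second objection concerns the denominator. The section does not say whether rates are per test, per woman screened or per resident. It also plans to search records for cases found outside screening, which would fit a population rate. With residents as the denominator, the formula above does not apply as shown. The mismatch still needs settling, because cases from controls outside 25-64 would have to be excluded or matched to a denominator that includes those ages.

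Third, standardisation removes any effect of reaching different ages, and wider coverage is a programme aim. This is a fair point and a reason to keep crude rates beside the standardised ones.

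A reader might go further and infer that the plan fixes a single unadjusted rate per period, or that the age shift will lower the HSIL rate and raise the cancer rate under HPV. The documents support neither. The first reads silence as a decision. The second needs age mixes and age-specific yields that the article does not give.

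**Conclusion.** The point holds in a limited form. As defined, the controls cover any age and the programme covers 25-64, and nothing stated brings the two into line for the rate comparison. At the article's national 20% under age 25, equal age-specific rates would give a crude ratio anywhere from about 1.24 to 0.91 over the assumed range of f. The bias vanishes if f is 1. Otherwise its direction depends on f, which may differ between precursor lesions and cancer, so the error need not be the same for both.

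The size rests on three assumptions: that the national 20% applies roughly to Indaiatuba, that rates are taken per test, and that f lies between 0 and 1.5. A change of mix within 25-64 could add to the bias or offset it, by an amount the article does not allow one to estimate. The weakness is in the analysis and can be corrected without altering the programme, so it should be settled before the periods are compared.

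**What to change.** 1. For this comparison, restrict both periods to women aged 25-64, and say so in the control group definition under Eligibility. This concerns the analysis set only, not who is offered screening.
2. In Data analysis, state that HSIL/AIS and cancer rates will be shown by age band for each period. Compare them after direct standardisation to the age distribution of the target population, or by a Poisson model with age band. Report crude rates alongside.
3. Use the age-specific rates, rather than one standardised rate, as inputs to the Markov model.
4. Report coverage by the same age bands, so that an overall 80% cannot hide low coverage at some ages.

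The cost is a few sentences and a little programming. It assumes that age is recorded in both data sources, which the article does not state for the control laboratory database. The census source cited under Sample size calculation could supply weights. It covers all 63,362 women aged 25-64, so using it for the SUS half assumes a similar age distribution there. What matters most is that both periods use the same weights.
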